**Table 4 Tab4:**
[figure not shown]
Power and sample size justification

### Recruitment {15}

The research team will post key study information on the National MS Society (NMSS) website, regional MS centers, the University of Iowa Hospital’s Neurology Clinic, [name], [name] Research Registry, social media advertisement, podcasts, posts, blogs, interviews, press releases, and other organizations to recruit study participants. Additionally, the study team will access the following study populations to recruit enough study participants to meet study recruitment goals: 1) send recruitment letters to neurologists at the University of Iowa and regional practices; 2) neurologists at the University of Iowa can invite their clinic patients; 3) mail posters and flyers/brochures to neurologists; 4) send emails to University of Iowa staff and students; 5) work with medical centers in Iowa to distribute flyers; 6) distribute brochures at professional and MS-related meetings; 7) post study information on NMSS website.

### Assignment of interventions: allocation

#### Sequence generation {16a}

Study participants will be randomized and evenly allocated at a 1:1:1 ratio to one of the following groups: MPE diet, or TROO ketogenic diet, or usual care control with DGA educational material, to remove bias from any staff performing study assessments responsible for the primary outcomes.

#### Concealment mechanism {16b}

The randomization table will be password-protected and accessible only to study RDNs and unblinded staff, ensuring it remains concealed from all blinded staff to uphold the integrity of the blinding process.

#### Implementation {16c}

Eligible participants will be informed of their assigned diet by the study RDNs during the baseline visit. Participants will be asked to discuss any diet-related concerns or questions with the RDNs or study coordinator to ensure that assessors and blinded staff remain unaware of their assignments.

### Assignment of interventions: blinding

#### Who will be blinded {17a}

Blinded staff include the PI, all co-investigators, and staff performing study visit assessments. Unblinded staff will include RDNs, study coordinator, and assigned research assistants working with data including, but not limited to, reviewing diet history questionnaires, Life Events (LE), study supplies, and adverse events (AE) reported by study participants. A member of the study team will inform study participants during the informed consent conversation that there will be blinded staff performing study assessments. In addition, statistical analysis of the study data will be performed independently by both a blinded and unblinded statistician.

#### Procedure for unblinding if needed {17b}

In the event of inadvertent unblinding by staff or study participant, the date and circumstance of the unblinding event will be documented. Following the unblinding, the research member of the team that was unblinded will not be allowed to perform any additional assessments on the unblinded study participant for the remainder of the study and a different assessor will be utilized at future study visits. In the case of a medical emergency, the study participant should inform all treating physicians what diet they were assigned for the study. Medical emergencies reported to the study team will be documented by unblinded staff and reported to the PI, Data and Safety Monitoring Board (DSMB), and IRB per Human Subject’s Office (HSO) reporting guidelines. In addition, once the final report has been reviewed by the DSMB, questions have been answered, and requested updates have been made, the DSMB will provide documentation that the PI and additional blinded staff may be provided with the randomized data.

## Data collection and management

### Plans for assessment and collection of outcomes {18a}

At baseline and every 6 months, participants will be sent links to complete web-based patient-reported outcomes assessments using validated questionnaires (Fig. 1). A custom, study-specific questionnaire will also be sent to participants every 3 months to monitor medical visits, perceived MS symptoms, life events affecting participation, and side effects of the dietary interventions. The following outcomes will be collected:

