#### Elimination and re-introduction phase (MPE group only)

At baseline (month 0), study participants assigned the MPE diet will be instructed to eliminate gluten, dairy, and eggs from their diet. In addition, at visit 2 (month 3), participants will also be instructed to eliminate all grains (including gluten-free), all legumes including peanuts and soy, and nightshade vegetables including tomatoes, potatoes, eggplants, and peppers for 3 months. After 3 months, study participants will be allowed to re-introduce one ingredient at a time, one ingredient per week. Study participants will be asked to keep a symptom diary and record any worsening mental or physical symptoms. If there are foods identified that cause a worsening of symptoms the study participant may remove the food item again. Participants may choose to re-introduce the food again if they desire to confirm whether the food is associated with worsening mental or physical symptoms. If symptoms again recur, the food may be eliminated from their diet for the remaining duration of the study.

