#### Nutrition counselling

Participants will have the opportunity to review the diet food guide for either the MPE diet or TROO ketogenic diet with the study dietitian via Zoom video conference. Dietary training to assist the participant in implementing the study diet will be given by an RDN who has experience with the study diet. The food guides provide prompts to eat the desired food groups and to avoid foods that are excluded in both intervention diets. Additional coaching calls will be arranged between the participants and the study team via telephone or Zoom. Two initial coaching calls following the nutrition counselling will be conducted 3–4 days after the Zoom meeting, as well as 7 days after the first call to answer questions as participants begin following their diet.

The conceptual basis for this intervention is informed by Social Cognitive Theory (SCT), which recognizes both the personal and environmental factors that influence health behavior change [29]. Personal factors addressed in SCT include: 1) behavioral capability, which is the understanding and skill to perform a behavior; 2) outcome expectancy, which is assigning a value to the outcomes of behavior change; 3) self-control, which is regulating and monitoring individual behavior; 4) self-efficacy, which refers to a person’s confidence in their ability to successfully perform a behavior; and 5) self-regulation, which facilitates people’s ability to control their behavior. Through this, individuals may create, alter, and commit to goals to achieve a desired outcome. The constructs of SCT will drive the sessions offered to our MS participants. Nutrition counseling techniques based on SCT, Self-Determination Theory [30], and Motivational Interviewing (MI) [31] will also be used to facilitate effective behavior change [32]. SDT focuses on intrinsic motivation and the factors that contribute to it, such as autonomy, competence, and relatedness, and suggests that providing opportunities for individuals to make choices (autonomy), develop skills and capabilities (competence), and foster positive relationships (relatedness) can lead to increased self-efficacy [33].

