### Monthly support

#### Usual care control group

During follow-up, participants in the usual care control group will receive monthly text messages, sent by Study Coordinator on behalf of the PI, along with emails containing recipes, cooking tips, and general information from DGA resources, as well as general information about MS. Brief video messages from the PI are provided as needed for participant re-engagement. In addition, engagement texts and emails tied to holidays, participant birthdays, and key study milestones will be sent. These monthly contacts and engagement messages are intended to support participant retention.

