### Intervention groups

#### Group support sessions

Both the TROO ketogenic and MPE diet groups will receive monthly group nutrition counseling sessions from the intervention RDNs to facilitate long-term diet adherence. Each intervention group will receive monthly live group behavioral support calls, using motivational interviewing, celebrating participant successes, addressing participants’ diet-related questions, to maintain participant engagement in the study. Participants will be invited to submit questions and comments ahead of time so that their concerns can be discussed even if they cannot attend live calls. The study PI will review questions submitted by the study participants in each group and create videos (specific to the intervention group) that address submitted questions. The calls will be recorded and hosted in the Canvas discussion platform. Monthly calls are expected to increase engagement but making them optional and hosting the recorded live coaching calls in the Canvas discussion platform reduces participant burden. Engagement texts and emails tied to holidays and participant birthdays and key study milestones will also be sent. Monthly contacts and engagement contacts are anticipated to enhance participant retention.

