### Frequency and plans for auditing trial conduct {23}

The DSMB will meet every six months in joint meetings with the Steering Committee to review cumulative safety and efficacy data from each study arm. The study team will also prepare and submit annual progress reports to the DSMB, summarizing enrollment status, adverse events, protocol deviations, and other relevant metrics. Following each DSMB meeting, the board will provide its recommendations and feedback directly to the PI, who will determine appropriate action in consultation with the Steering Committee. In addition to these formal oversight procedures, the PMG, comprising the PI, study coordinator, senior investigators, RDs, and research staff, meet weekly to monitor ongoing trial operations, address logistical or compliance issues, and ensure that the trial is progressing according to the established timeline and regulatory requirements.

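### Mild, self-reported adverse events are at risk of being found more readily in the diet arms than in usual care, because the side-effect topic and the live contact are tied to the diets

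*Protocol article*

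**What the plan says.** - **Common survey.** Under Plans for assessment and collection of outcomes {18a}: "A custom, study-specific questionnaire will also be sent to participants every 3 months", its aim being "to monitor medical visits, perceived MS symptoms, life events affecting participation, and side effects of the dietary interventions".
- **Diet arms.** Participants are asked to book a Zoom session with the registered dietitian nutritionists (RDNs) to go over the diet. After that, "Two initial coaching calls following the nutrition counselling will be conducted" (Nutrition counselling). In addition, "Both the TROO ketogenic and MPE diet groups will receive monthly group nutrition counseling sessions from the intervention RDNs to facilitate long-term diet adherence", and the same section (Group support sessions) states that "Each intervention group will receive monthly live group behavioral support calls"; attendance is optional.
- **Modified Paleolithic elimination (MPE) arm only.** In the re-introduction phase, "Study participants will be asked to keep a symptom diary and record any worsening mental or physical symptoms".
- **Ketogenic (TROO) arm only.** A ketone and glucose meter is supplied for diet tracking, and RDNs can see the readings.
- **Usual care.** Controls carry on with their own diet and may use the guideline material as much or as little as they wish. Under Monthly support, "participants in the usual care control group will receive monthly text messages" and emails.
- **Staff and oversight.** RDNs are unblinded, and unblinded staff also work with adverse events (AEs) that participants report (Who will be blinded {17a}). The Data and Safety Monitoring Board (DSMB) meets every six months "to review cumulative safety and efficacy data from each study arm".

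**The concern.** A by-arm safety review is informative only if an event of a given kind has a similar chance of being noticed and recorded in each arm. Here the one explicit side-effect topic refers to an intervention that controls do not have. Diet-arm participants also speak regularly to unblinded staff, to whom a symptom can be mentioned in passing, and one arm writes symptoms down. For mild events, a real excess on a diet and closer observation of that diet could then look the same. That bears on the DSMB's reviews and on the article's stated expectation that the diets will be safe over the long term. Later analysis cannot recover a control-arm event that was never asked about.

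**Working it through.** **Inputs.** The article gives no AE rate and no share of AEs captured, so it states no figure on this point to reproduce. The contact schedule comes from the sections cited above. Group size is used only in step 4, and it does reproduce: 36 / (1 − 0.33) = 53.7, rounded up to 54; 3 × 54 = 162.

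**Step 1. Scheduled contact over 24 months.**

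| | Each diet arm | Usual care |
|---|---|---|
| 3-monthly questionnaires after baseline | 24 / 3 = 8 | 8 |
| In-person visits after baseline (months 3, 24) | 2 | 2 |
| Other scheduled live contacts | up to 1 + 2 + 24 = 27 | 0 |
| Symptom diary | MPE only | none |
| Ketone and glucose meter | TROO only | none |

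The 27 are one Zoom diet session, two coaching calls and about 24 optional monthly sessions, taking the monthly counselling sessions and support calls as one series. Controls have about 24 monthly messages instead.

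**Step 2. Which events are exposed.** The listed AE types, set against the channels that all arms share:

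- *Relapse:* the questionnaire's MS-symptom and medical-visit topics, shared neurology notes, and reports of treatment for relapses. Little exposed.
- *Hospitalization, or infection leading to a visit:* the medical-visit topic and shared clinical notes. Little exposed.
- *Abnormal laboratory value:* blood is drawn at every in-person visit, without restriction by arm. Little exposed.
- *Symptom worsening without a visit:* the MS-symptom topic covers all arms, but the MPE diary adds to it in one arm. Partly exposed.
- *Gastrointestinal complaint without a visit or treatment:* diet-arm participants are asked directly. No topic evidently asks a control. Most exposed.

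**Step 3. Illustrative size.** Assume equal true event rates. Let c be the share of events captured through the common questionnaire in every arm, and f the share of the remainder picked up through the extra diet-arm contacts. The observed rate ratio, diet to control, is [c + f(1 − c)] / c. With c = 0.60:

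- f = 0: 0.60 / 0.60 = 1.00
- f = 0.25: (0.60 + 0.10) / 0.60 = 0.70 / 0.60 = 1.17
- f = 0.50: (0.60 + 0.20) / 0.60 = 0.80 / 0.60 = 1.33
- f = 0.75: (0.60 + 0.30) / 0.60 = 0.90 / 0.60 = 1.50

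Other assumed pairs widen the range: 95% against 90% gives 0.95 / 0.90 = 1.06, and 90% against 50% gives 0.90 / 0.50 = 1.80.

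**Step 4. If a reader tested the difference.** The article specifies no AE test. Suppose one is applied to one diet arm against control: 54 per arm, two-sided 0.05, normal approximation, assumed true risk of 40% in both arms.

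| Capture, diet vs control | Observed risk | Chance of a significant excess on diet |
|---|---|---|
| 90% vs 80% | 36.0% vs 32.0% | about 6% |
| 90% vs 70% | 36.0% vs 28.0% | about 14% |
| 90% vs 50% | 36.0% vs 20.0% | about 46% |

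With equal capture the chance in that direction would be 2.5%. Over true risks of 20% to 60%, the 90% vs 70% case runs from about 8% to 24%.

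**The case against.** The strongest reply is that a reader could easily infer too much.

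- *That the questionnaire is the only common channel.* It is not. Eligibility requires every participant to share primary care and neurology notes. All participants report concomitant treatments, including those for AEs and relapses. Blood is drawn in all arms, and retention messages to all include check-ins. Three of the questionnaire's four topics are arm-neutral.
- *That AEs are actively sought through calls and the diary.* No section says so. The calls serve questions, adherence and engagement. The diary serves decisions about re-introduced foods, and nothing says that it feeds the AE forms. Nor are the control messages described as one-way.
- *That the comparison is biased, and most so for MPE.* The survey items and AE form are not shown and no between-arm AE test is planned. TROO has its own extra monitoring, so no ranking of the two diets follows.
- *That unequal contact is itself a flaw.* It is part of a usual-care comparison, and the article justifies it.

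These replies limit the point to a risk, and mainly to mild self-reported events. They do not remove it. The purpose of the survey and the contact schedule are stated in the article, and no formal test is needed for unequal ascertainment to mislead a by-arm review. A symptom mentioned on a call does reach unblinded staff, and the article describes no rule on how its source is recorded.

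**Conclusion.** The point holds as a risk of differential ascertainment for mild, self-reported AEs that lead to no medical visit, chiefly gastrointestinal symptoms and minor symptom worsening. It rests on two documented facts: a diet-framed side-effect topic put to all arms, and live contact (plus the MPE diary) that only the diet arms have. It does not extend to relapses, hospitalizations or laboratory values to the same degree. The size is unknown. The ratios of 1.17 to 1.50 depend entirely on assumed capture of 70% to 90% against 60% and equal true rates; they show what is possible and estimate nothing. The documents do not support saying that the AE comparison is biased, only that a modest apparent excess on diet in these mild events could not be told from closer observation.

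**What to change.** 1. **Survey.** In the remaining 3-monthly questionnaires, add one arm-neutral question, identical in all three arms: any new or worsened health problem since the last survey. Keep the diet side-effect item for tolerability in the diet arms.
2. **Source.** Record the source of each AE (questionnaire topic, clinical notes, treatment report, blood test, call, diary), retrospectively where it is known.
3. **Tables.** Beside the table of all AEs, give the DSMB and the final report a by-arm table restricted to the common channels: arm-neutral questionnaire topics, clinical notes, treatment reports and scheduled blood tests. Use it for comparisons with control. List events found only through diet-arm contacts or the MPE diary separately.

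**Cost.** One survey item, one database field with some back-filling, and one extra table. The comparative table will hold fewer events, and earlier surveys lack the neutral question. Recruitment ended on July 22, 2024 and the article appeared on October 27, 2025, about 15 months later. A participant enrolled on the last day would then have at most the month 18, 21 and 24 surveys left, and many others have none. Most of the benefit therefore comes from the source field and the second table. The report should say that the control rate of mild events before the change is weakly measured.

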### Patient-reported outcomes

*MSQoL-54:* The MSQoL-54 questionnaire is a 54-item measure of physical- (35 items) and mental health (18 items)-related QoL, including 12 subscales. Higher scores indicate better QoL [35]. A 5-point change is considered clinically significant [36, 37]. In people with MS, the subscales have good internal consistency and test–retest reliability scores [35].*Fatigue Severity Scale (FSS)*: The FSS is a nine-item questionnaire in which participants are asked to rate how fatigue affects their activities of daily life. Participants with a mean value of ≥ 4 are considered fatigued [38]. The FSS is a reliable and sensitive measure and has demonstrated internal consistency and discriminative properties among people with MS. Clinically meaningful reduction is defined as a decrease in score of at least 0.45 [39].*Modified Fatigue Impact Scale (MFIS)*: The MFIS is a 21-item measure of fatigue’s effects on daily physical (9 items), cognitive (10 items), and psychosocial (2 items) function, where higher scores reflect a greater impact of fatigue [40]. Internal consistency is very good. Clinically meaningful reduction is defined as a decrease in score of at least 4.0 [39].*Hospital Anxiety and Depression Scale (HADS):* The HADS is a 14-item self-report measure with two subscales assessing anxiety and depression [41]. A score of 8 or above on either subscale indicates clinically elevated symptoms of anxiety or depression. Clinically meaningful reduction is defined as a decrease in score of at least 1.5 for the Anxiety portion of HADs and 0.5 for the Depression portion of HADS [42]. The HADS has high sensitivity and specificity in people with MS [43–45].*Patient Determined Disease Steps (PDDS)*: Disease status will be monitored with the PDDS, which was originally developed as a patient-reported surrogate to the Disease Steps [46]. The PDDS has nine levels of disease burden ranging between 0 (normal) to 8 (bedridden) [47] and can be converted into EDSS scores [48] as well as classifications of mild, moderate, or severe disability [49]. The PDDS has been validated to several measures of disability in MS [50]. A clinically meaningful change in PDDS is defined as a change in score of 0.99 points [51].

Functional disability will be assessed by:*MS Functional Composite (MSFC) (months 0, 3, and 24):* The MSFC is a validated measure of physical and cognitive function in MS that includes measures of upper extremity coordination (NHPT), gait speed (T25FW), and cognition (SDMT-O) [57, 66]. Raw NHPT, T25FW, and SDMT-O values will be converted to baseline-referenced z-scores and averaged to obtain an overall MSFC score [57]. The MSFC has good construct and concurrent validity; however, there is no recognized clinically significant change cut point [67]; though one study defined a clinically significant change as 0.5 MSFC points [68].

Ocular function will be assessed using:*Dominant eye test (month 0):* This is a simple procedure used to determine which of a person’s eyes is dominant. The dominant eye provides a slightly greater degree of input to the visual part of the brain and relays information more accurately [69].*Visual acuity:* The study participant will sit 6 feet from the chart, cover one eye with a handheld ophthalmic eye occluder (starting with testing right eye), and starting at the top, slowly read the chart out loud, starting with the biggest row of letters and moving down to smaller rows until letters are not seen clearly. The test is repeated for the other eye. If the participant does not reach 20/40 visual acuity, the trial will be repeated using a pinhole eye occluder.*Contrast sensitivity:* The study participant will repeat the procedures of the visual acuity test for each eye with lighter charts at 2.50% and 1.25% contrast.*Critical flicker fusion (CFF):* This is a validated measure to assess optic nerve function in the setting of MS. Improvement by at least 2 Hz is considered clinically meaningful change [70].*Optical coherence tomography (OCT) (months 0 and 24):* This test measures the thickness of the retinal nerve fiber layer and the retinal ganglion cell layer. We will correlate thickness of these layers, CFF threshold, and low contrast visual acuity (LCVA) to assess changes in ocular measurements over the course of the study and between groups.

Disease activity will be assessed by:

*Brain Magnetic Resonance Imaging/Spectroscopy (MRI/S) (months 0 and 24)*: *MRI*: Two of the primary markers for MS progression on MRI images are lesion burden based on FLAIR hyperintensities [71–73] and changes in T1-weighted brain tissue volumes [72, 73].*Magnetic resonance spectroscopy (MRS)*: The current study will include single voxel MRS in frontal lobe white matter to identify brain metabolite changes over time. The ^1^H MRS data will be analyzed using the LCModel [74]. Water suppressed and non-water suppressed data will be analyzed to generate absolute concentrations after performing phase and eddy current correction. Concentration measurements for N-acetyl aspartate (NAA), glutamate + glutamine (Glx), total creatine (Cr + PCr), total choline (tCho), myo-inositol (mI), and lactate will be obtained from the ^1^H data.

Nutritional safety of the dietary interventions will be monitored by:*Blood measurements:* Blood will be collected at each in-person study visit. The UI Department of Pathology will analyze whole blood, serum or plasma for creatinine, aspartate aminotransferase, complete blood count, glucose, β-hydroxybutyrate, insulin, hemoglobin A1c, lipids, and vitamin D at months 0 and 24 visits. Hemoglobin Alc, lipids, and glucose will be analyzed at month 3 visits.

Exploratory analyses.*Saliva biospecimens*: Specimens will be collected at months 0, 3, and 24 study visits and frozen for future microbiome analysis.*Blood samples:* Samples will be collected at months 0, 3, and 24 study visits and frozen for future mechanistic analyses.

